#### Perceived quality of the message

Three items evaluate whether the message is credible, convincing, and persuasive. Response options are on a 7-point Likert scale.

#### Positive outcome expectation

Eight items will be created ad hoc for this research evaluating positive outcome expectations regarding the participant himself (4 items) and his family members (4 items). Response option will be on a 5-point Likert scale.

#### Action self-efficacy

According to Schwarzer & Luszczynska’s [17] indications, self-efficacy will be assessed through three items as the capability of keeping up with the behavior, by implementing coping strategies. Response option will be on a 5-point Likert scale.

#### Benefit for genetic test

A 5-digit semantic differential will be applied to measure the perceived benefit for genetic tests. Examples of the proposed adjectives are important, relevant, useful, benefic.

#### Intention to undergo genetic testing

The intention of undergoing genetic testing is measured through three items evaluating the urge to engage the behavior. An example of item is: "In the next few months, do you have the intention of planning a genetic screening?". Response options are on a 5-point Likert scale.

#### Coping self-efficacy

Three items created ad hoc for the present research evaluate whether the individual feels to be capable of tackling the possible obstacles and difficulties that could make it difficult to undergo a genetic screening. Response options are on a 5-point Likert scale.

#### Action planning

Three items developed ad hoc for the present research will ask if the participant has planned when, how, and where to undergo the genetic test for BRCA1/2 mutations. Response option will be on a 4-point Likert scale.

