### Hypotheses

We hypothesize the following relationships (Fig 1 shows the tested model):

HP1: higher risk perception, positive outcome expectations and action self-efficacy longitudinally predict the intention to undergo genetic test for BRCA germline mutations.HP2: higher health risk attitude and low intolerance to uncertainty have a longitudinal influence on predicted higher intention, planning and action initiation.HP3: higher intention and coping self-efficacy longitudinally predict higher planning.HP4: higher planning (i.e., action planning, coping planning) and coping self-efficacy longitudinally predict higher action initiation.Based on results by Rauscher et al. [14] and Hallowell and colleagues [50], we formulated a research question: (RQ1) is there any difference between personal outcome expectations and family outcome expectations in their association with intention?HP5: family-referred narrative gain framed message (vs. self-referred narrative gain framed message) will produce greater intention and action to undergo genetic testing for *BRCA 1/2* germline mutations in at-risk men.

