#### Time 1 assessment

All participants will complete the T1 assessment, via an online survey which will be available for a two-week period. The T1 measures will include demographic, health status, risk perception, health risk aversion, and intolerance of uncertainty. After this evaluation, participants will be randomized and exposed to one message. A manipulation check, the evaluation of the perceived quality of the information presented on the messages, positive outcome expectations, action self-efficacy, benefit for genetic test will be then collected. The constructs of trust in doctors and health literacy included in the original study protocol approved by the Ethical Committee have been not integrated here.

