#### Time 2 assessment

The original study protocol approved by the Ethical Committee included a T2 assessment with questions on intention to undergo germline genetic testing and evaluation of the quality of the message content, and a subsequent (3–4 weeks later) T3 with coping self-efficacy, action planning, and coping planning. Since the HAPA model does not state that there should be a waiting time between the measurement of the intention and the coping/action planning, we collapse T2 and T3. Therefore, one-two weeks after the administration of T1, via an online survey, participants reply to questions on intention to undergo germline genetic testing, coping self-efficacy, action planning, and coping planning.

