### T3 measures

#### Action

Information on the action initiation (i.e., genetic test for *BRCA1/2* germline mutations) will be collected when the participant takes the appointment for the genetic test and receives the test.

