**Hypothesis 1.** Predictors will be: risk perception, positive outcome expectations, action self-efficacy. Covariates: demographic, health status. Outcome variable will be: intention to undergo genetic test for BRCA germline mutations.**Hypothesis 2.** Predictors will be: health risk attitude, intolerance to the ambiguity. Covariates: demographic, health status. Outcome variables will be: intention to undergo genetic test for BRCA germline mutations, action and coping planning, action initiation.**Hypothesis 3.** Predictors will be: intention to undergo genetic test for BRCA germline mutations, coping self-efficacy. Covariates: demographic, health status. Outcome variables: action and coping planning.**Hypothesis 4.** Predictors will be: action and coping planning. Covariates: demographic, health status. Outcome variable: action initiation.**Research question 1.** Predictor variable: positive outcome expectations (personal vs family). Outcome: intention to undergo genetic test for BRCA germline mutations.**Hypothesis 5.** Predictor variable: treatment/message (family-referred narrative gain framed message vs. self-referred narrative gain framed message). Outcome variables: intention and action to undergo genetic testing for *BRCA 1/2* germline mutations.

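### HP4 relates planning at T2 to action initiation without separating men who booked or were tested before T2, so its predictor and outcome can overlap

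*Protocol article*

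**What the plan says.** All references are to the protocol article.

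- **Hypotheses, HP4:** "higher planning (i.e., action planning, coping planning) and coping self-efficacy longitudinally predict higher action initiation".
- **Time 1 assessment:** the message is shown at T1, after the baseline measures: "After this evaluation, participants will be randomized and exposed to one message".
- **Time 2 assessment:** intention, coping self-efficacy and both planning scales are asked "one-two weeks after the administration of T1, via an online survey".
- **Action planning:** three ad hoc items on a 4-point scale "will ask if the participant has planned when, how, and where to undergo the genetic test for BRCA1/2 mutations".
- **Time 3 assessment:** collection of action data opens when T2 closes and runs for three months. Action initiation is glossed as the genetic test.
- **T3 measures, Action:** the information "will be collected when the participant takes the appointment for the genetic test and receives the test", with the same gloss.
- **Statistical analyses, Hypothesis 4:** "Predictors will be: action and coping planning. Covariates: demographic, health status. Outcome variable: action initiation".

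The stated exclusions from analysis are failure of the manipulation check and non-completion of T1 and T2. Table 1 has an exclusion worded around a detected BRCA1/2 screening result, but no criterion mentions a man who already holds an appointment. No planning or booking measure before T2 is described.

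**The concern.** A claim that planning predicts later action needs a risk set of men who have not yet acted when planning is measured. The article leaves one to two weeks between the message and T2, and a man moved by the message can book in that time. An appointment settles when and where he will be tested, and largely how, so at T2 he would probably rate himself high on action planning. Taking the appointment is also one of the two moments at which action information is recorded. His high planning score would then partly reflect action already begun.

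The article does not say whether action means the appointment, the test or both, nor how an appointment made before the window opens is coded. HP4 can be distorted under either coding, in opposite directions. At stake is the reading of the planning-to-action path, one of the HAPA paths the study sets out to test.

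**Working it through.** The article gives no figure on this point to reproduce. The check has two parts.

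**1. The passages side by side**

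| Reading of action | Man who books before T2 and is tested after T2 | Effect on HP4 |
|---|---|---|
| Appointment counts, pre-T2 appointments included | The appointment behind his planning score is also his action | Inflated; predictor and outcome coincide for him |
| Test counts, received after T2 | Acted; appointment and test are two ordered events | Association raised by men who had already taken the first step |
| Pre-T2 booking treated as outside the window, man coded as not acting | High planning, no action | Biased slightly downward |

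The article does not choose among these rows.

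**2. How large the distortion could be**

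From the article: N=132 (result of the power calculation) and N=264 (planned enrolment), and three items on a 4-point scale.

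Assumed, because the article gives no figure:
- share *b* booked before T2: 0, 2, 5 or 10%;
- action rate among unbooked men *a* = 20%, unrelated to planning;
- planning in unbooked men centred at 2.2, with a person SD of 0.7 and an item SD of 0.6;
- booked men at 4;
- share *q* of booked men counted as acting: 1, 0.8 or 0.

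Formula for the expected correlation of planning with action:

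- cov = b(1−b)(4−2.2)(q−a)
- p = bq + (1−b)a, and SD of action = √[p(1−p)]
- variance of planning = (1−b)s² + b(1−b)(4−2.2)², with s² = 0.7² + 0.6²/3 = 0.61 before rounding to the 4-point scale
- r = cov / (SD of action × SD of planning)

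For b=5%, q=1:
- cov = 0.0475×1.8×0.8 = 0.0684
- p = 0.05+0.19 = 0.24, SD 0.427
- variance of planning = 0.5795+0.1539 = 0.7334, SD 0.856
- r = 0.0684/(0.427×0.856) = 0.187

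For b=5%, q=0:
- cov = 0.0475×1.8×(−0.2) = −0.0171
- p = 0.19, SD 0.392
- r = −0.0171/(0.392×0.856) = −0.051

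The simulation rounds and truncates the items to 1–4, which shifts these slightly. It used 2,000 replicates per cell and a two-sided 5% test of Pearson's r:

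| b | q | mean r, N=132 | p<0.05, N=132 | p<0.05, N=264 |
|---|---|---|---|---|
| 0% | – | about 0 | 4% | 4–5% |
| 2% | 1 | 0.09 | 19% | 33% |
| 5% | 1 | 0.19 | 61% | 86% |
| 10% | 1 | 0.33 | 95% | 99.8% |
| 2% | 0.8 | 0.07 | 13% | 22% |
| 5% | 0.8 | 0.15 | 43% | 66% |
| 10% | 0.8 | 0.25 | 81% | 98% |
| 5% | 0 | −0.05 | 7% | 11% |
| 10% | 0 | −0.10 | 16% | 31% |

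In men, 2% is about 3 of 132 or 5 of 264, and 5% is about 7 of 132 or 13 of 264. The test is a simple correlation with action planning. It leaves out coping planning and the covariates of the HP4 model, so the shares are illustrative.

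**The case against.** The strongest case on the other side has four parts.

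*The window.* The Time 3 assessment section opens action collection at the end of T2, so on a literal reading a pre-T2 appointment is not recorded as action. This stands against any claim that such a man is certainly counted. It does not remove the problem: the section says when data are collected, not what becomes of a man who booked earlier. If he is coded as not acting, HP4 is biased the other way.

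*The order of events.* Both sections gloss action as the genetic test. A man who has fixed the details by T2 and is tested later then shows plan followed by behaviour, as HP4 describes. This stands for a test-only outcome. A reader might infer that predictor and outcome are simply one event, but the article supports that only if the appointment alone counts and pre-T2 appointments are included. It states neither.

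*The simulation.* It assumes top planning scores and action for early bookers, and the driving rate is not in the article. This stands. With no early booking there is no inflation, and at 2% and N=132 the share significant is 19%. A reader might infer that HP4 can hardly fail; the figures do not show that.

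*Detail left to a fuller document.* An article may leave analysis sets to the SAP. But the items, outcome events, exclusions and HP4 predictors are all stated here, and together they allow the overlap. If neither a T2 booking question nor appointment dates exist, a later SAP cannot identify these men. Collecting information at the appointment may supply dates, but the article does not say so.

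**Conclusion.** The point holds as a flaw in HP4's risk set and outcome definition. Men who booked or were tested between the message and T2 are not identified, the event that defines action is not fixed, and their coding is open. If they are counted as acting, the HP4 association is inflated: at assumed early-booking rates of 2–10%, with no true effect in other men, about 19–95% of trials are significant at N=132 and 33–100% at N=264. If they are coded as not acting, r is about −0.05 to −0.10 at rates of 5–10%. These sizes rest on assumed booking and action rates and on early bookers scoring at the top, which is likely but not guaranteed by the item description.

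A reader might go further and say that planning will appear to cause testing. The documents do not support that: HP4 is worded as longitudinal prediction, and neither the size nor the sign of the bias can be fixed from the text. HP4 is also not the primary hypothesis. HP5 is, and a booking after randomisation is a legitimate outcome there. This is a cheap improvement worth making, not a threat to the primary comparison.

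**What to change.** 1. Reconcile the Time 3 assessment and Action sections so that HP4 action is one defined event, first occurring after T2, and say how earlier appointments are treated.
2. At T2, before the planning items, ask whether an appointment has been made or the test done, and record the dates.
3. Run the main HP4 model in men with neither at T2.
4. Add a sensitivity analysis that keeps the early bookers and takes receipt of the test after T2 as the outcome. Men already tested by T2 cannot have that event, so report their number separately.
5. Keep all men in HP5.

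The cost is one short online question with dates and a few sentences in the analysis section. The main HP4 model loses a few men and some range at the top of the planning score, possibly those in whom planning led to action fastest, which could weaken a true association. The sensitivity analysis shows how much this matters.

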#### Coping planning

Four items developed ad hoc for the present research will ask how much the participant thinks to encounter in planning the action. Response option will be on a 5-point Likert scale.

### T3 measures

#### Action

Information on the action initiation (i.e., genetic test for *BRCA1/2* germline mutations) will be collected when the participant takes the appointment for the genetic test and receives the test.

### Primary and secondary outcomes

The primary objective of the present research project is to compare self-referred message to family-referred message promoting men’s adherence to evidence-based guidelines on *BRCA1/2* germline genetic testing. The primary clinical objective is to determine what is the best communication strategy to inform men who are at risk to have a germline mutation because they are relatives of women with such a mutation. The primary hypothesis of the study is that family-referred narrative gain framed message (vs. self-referred narrative gain framed message) will produce greater intention and action to undergo genetic testing for *BRCA 1/2* germline mutations in at-risk men.

The secondary objective is to assess men’s characteristics (demographic information, psychological characteristics, health status) that may explain the intention and the action to undergo genetic test for BRCA germline mutations.

### Ethical considerations

Ethical approval has been acquired from the local ethics committee of the IEO (approval number R1249/20-IEO 1314). Participation is voluntary. All data will be collected in a pseudo-anonymized form. Data will be analyzed in an anonymous form. Data will be treated confidentially and used only by the collaborators in the present study for scientific purposes. No adverse effects are expected for participants; in case of necessity, personal contact of the main researchers will be shared with them.

### Statistical analyses

Data exclusion: The answers to the manipulation check will be analyzed before the main analyses to see whether participants have read the message until the end, understood, and recalled the content.

Missing data: presence of missing data will be checked before conducting the main analyses. If a subject does not complete T1 and T2 that subject will be excluded from the analysis.

Normality of the data will be checked before conducting the main analyses. Non-normality will be handled applying either non-parametric tests or SEM with estimator for non-normal distribution.

Statistical analyses will be performed in SPSS version 25 and the *Lavaan* and *SemPaths* packages in RStudio software.

Preliminary analysis: Pearson’s r correlations among variables.

Main analyses: the hypotheses 1, 2, 3, and 4 will be tested either using structural equation modeling (SEM) or multiple regressions. Research question 1 will be tested either using structural equation modeling (SEM) or ANOVA. In case of non-normality in the data, WLSMV will be applied and the Satorra-Bentler scaled test statistic and robust standard errors were used. In the model specification, the factor loading of the first indicator of each latent variable will be set to 1. The following goodness-of-fit indices will be used to evaluate model-data correspondence: the Chi-square value, the Comparative Fit Index (CFI), and the Root Mean Square Error of Approximation (RMSEA). The model will be considered as acceptable when the CFI is higher than .90 and close to .95 and when the RMSEA is .08 or less. Finally, modification indices and the matrix of standardized correlation residuals will be inspected for potential improvement of model fit. Direct, indirect (or mediate), and total effects were also estimated. To test hypothesis number 5 an ANCOVA will be applied.

**Hypothesis 1.** Predictors will be: risk perception, positive outcome expectations, action self-efficacy. Covariates: demographic, health status. Outcome variable will be: intention to undergo genetic test for BRCA germline mutations.**Hypothesis 2.** Predictors will be: health risk attitude, intolerance to the ambiguity. Covariates: demographic, health status. Outcome variables will be: intention to undergo genetic test for BRCA germline mutations, action and coping planning, action initiation.**Hypothesis 3.** Predictors will be: intention to undergo genetic test for BRCA germline mutations, coping self-efficacy. Covariates: demographic, health status. Outcome variables: action and coping planning.**Hypothesis 4.** Predictors will be: action and coping planning. Covariates: demographic, health status. Outcome variable: action initiation.**Research question 1.** Predictor variable: positive outcome expectations (personal vs family). Outcome: intention to undergo genetic test for BRCA germline mutations.**Hypothesis 5.** Predictor variable: treatment/message (family-referred narrative gain framed message vs. self-referred narrative gain framed message). Outcome variables: intention and action to undergo genetic testing for *BRCA 1/2* germline mutations.

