### Sample size and power calculation

Participants will be 264 males, relatives of women with BRCA1 and/or BRCA2 germline mutations who are patients of the Division of Cancer Prevention and Genetics at the European Institute of Oncology (IEO) in Milan. The IEO is a specialized Hospital and an internationally recognized Cancer Center located in Italy working on research, prevention, diagnosis, and treatment of cancer.

The sample size is determined through an a priori power analysis using GPower 4.0 [51]. Among the imputed parameters it was chosen to include partial η2 = .05, alpha lower than .05, power d (1-B) = .70. Considering that Luszczynska et al. [52] found a η2 = .01, η2 = .05 is a prudential choice. Two groups, corresponding to the two experimental conditions of the study, and 7 covariates were included. The final estimated number of participants is 132, 66 in each group. It should be noted that changing the number of covariates does not change the total number of participants. As of the date of submission of this research plan for preregistration, the data have not yet been collected, created, or realized.

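### The normality check does not exempt hypothesis 5, so the primary ANCOVA on intention may be replaced after the outcome data are seen, with two fallbacks left open

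*Protocol article*

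**What the plan says.** All references are to the protocol article.

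- **Statistical analyses**, before any hypothesis is discussed: "Normality of the data will be checked before conducting the main analyses". The next sentence gives the consequence: "Non-normality will be handled applying either non-parametric tests or SEM with estimator for non-normal distribution".
- The same section, under main analyses: "To test hypothesis number 5 an ANCOVA will be applied". SEM is offered as an alternative for hypotheses 1-4 and research question 1, but not for hypothesis 5.
- **Primary and secondary outcomes** makes the content of hypothesis 5 (family-referred versus self-referred message, on intention and action) the primary hypothesis.
- **Intention to undergo genetic testing**: "The intention of undergoing genetic testing is measured through three items", each on a 5-point scale. No scoring rule is given.
- **Sample size and power calculation**: "Two groups, corresponding to the two experimental conditions of the study, and 7 covariates were included", so the calculation is for a covariate-adjusted comparison.
- The list of hypotheses that closes the statistical section names demographic and health-status covariates for hypotheses 1-4 and none for hypothesis 5.

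The article does not say whether the check applies to raw scores or residuals, which fallback applies to hypothesis 5, or which non-parametric test is meant.

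**The concern.** The normality rule is general and stands ahead of the main analyses. Hypothesis 5 is one of these and is not carved out. Read as written, the method for the primary comparison depends on how the outcome data look, and a failed check leads to two different kinds of analysis with no rule for choosing between them.

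Three things are at stake. The primary test is not fixed in advance. A switch may change what is estimated, from an adjusted mean difference to a rank-based contrast or a latent-variable path. And if the replacement is unadjusted, the power calculation with seven covariates no longer describes the test that is run.

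The rule also cannot work for action, the other outcome of hypothesis 5. Whether the genetic test is taken is a yes/no outcome, for which neither a normality check nor ANCOVA is suitable.

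**Working it through.** **Step 1. The plan's own power figure.** Inputs from Sample size and power calculation: "it was chosen to include partial η2 = .05", "alpha lower than .05", power .70, two groups, seven covariates. With f² = .05/.95 = .0526, λ = N·f², and F on 1 and N − 2 − 7 degrees of freedom, power .70 is reached at N = 120, not at the stated 132 ("The final estimated number of participants is 132, 66 in each group"). At N = 132, λ = 132 × .0526 = 6.95 and power is 74.4%. At the planned 264, λ = 13.89 and power is 96.0%. The gap between 120 and 132 is conservative and does not affect this point.

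**Step 2. How often would the check fail?** Assumption: intention is the sum or mean of its three items. The sum runs from 3 to 15, so it has 15 − 3 + 1 = 13 possible values on a bounded scale. Two sets of simulations were used: 1,000 runs per setting with item loadings .7-.9, and 1,500 runs per setting with item correlation .6 and seven covariates of latent R² 0, .2 or .4. A third set (1,000 runs, loadings .8) applied a descriptive rule, flagging absolute skewness or excess kurtosis above 1; that cut-off is an assumption.

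| Check | Symmetric responses | Mild skew | Ceiling |
|---|---|---|---|
| Shapiro-Wilk, raw score, N = 132 | 87-95% | 100% | 100% |
| Shapiro-Wilk, raw score, N = 264 | 100% | 100% | 100% |
| Shapiro-Wilk, ANCOVA residuals, N = 132-264 | 4-11% | 42-100% | 98-100% |
| Descriptive rule | at most 7% | at most 7% | 98-100% |

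The residual row is from the second set; the third gave 4-15% with symmetric responses. The outcome of the check thus depends mainly on what is checked and how.

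**Step 3. Does ANCOVA need the protection?** Its type I error was 3.8-5.3% with robust (HC3) errors in the first set and 3.9-6.2% over all response shapes in the second (simulation error about 1.1 points). Non-normality of this kind gives no reason to leave it.

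**Step 4. What would an unadjusted rank test cost?** Hold the adjusted effect at partial η² = .05. For Mann-Whitney, replace N by .955 N (its assumed relative efficiency), drop the covariates, and replace f² by f²(1 − R²). Then 132 becomes 126 and 264 becomes 252. The R² values are assumptions; the article gives none.

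| Covariate R² | λ at N = 132 | Power | Loss against 74.4% | λ at N = 264 | Power | Loss against 96.0% |
|---|---|---|---|---|---|---|
| 0 | 6.63 | 72.4% | 2.0 | 13.26 | 95.2% | 0.8 |
| .2 | 5.31 | 62.8% | 11.6 | 10.61 | 90.1% | 5.9 |
| .4 | 3.98 | 50.8% | 23.6 | 7.96 | 80.2% | 15.8 |

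The second set of simulations puts R² on the latent scale and sets the effect differently, and shows a smaller loss. At N = 132 and R² = .4, Mann-Whitney against ANCOVA was .675 against .830 (symmetric), .684 against .801 (mild skew) and .603 against .657 (ceiling). At R² = 0 it was .686 against .672, .675 against .648 and .607 against .543, so no weaker. Rank ANCOVA, which is non-parametric and adjusted, stayed within about 2 points of ANCOVA or exceeded it.

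**The case against.** The strongest reply is that hypothesis 5 is not gated at all. The sentence assigning ANCOVA to it carries no condition, and the detailed provisions for non-normality (WLSMV, Satorra-Bentler) sit with the SEM hypotheses. That reading is possible, but the general rule precedes all main analyses and excludes none, so the text must be settled one way or the other.

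A reader might infer something stronger: that the check will almost always fail and the primary test will become a weaker, unadjusted one. The article does not support this.

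- SEM is the other named fallback and can keep covariates, as can rank ANCOVA.
- Near-certain failure belongs to a formal test on raw scores or to a strong ceiling. The article names no test and does not exclude residuals. It gives no scoring rule either, so intention might be modelled as a latent variable with ordinal indicators.
- Weaker depends on covariates that explain something. No baseline intention is collected and none are named for hypothesis 5. In one simulation with ceiling responses, Mann-Whitney matched ANCOVA even at R² = .2 (.459 against .455 at N = 132).
- Inflated error is not shown either. The gated procedure had type I error of 3.7-6.2%, within simulation error of 5%. Only free choice of the smaller p-value raised it, to about 6-8%.

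It is also fair that naming the normality test and its threshold can be left to an analysis plan. What remains is a rule the article does state, which lets the primary method change on sight of the outcome.

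**Conclusion.** The point holds in a limited form. As written, the primary test of intention may be replaced after the outcome data are seen, and the choice of replacement is open. Failure of the check is likely (about 87-100%) if a three-item score is tested formally on its raw values, and uncertain otherwise.

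The power loss applies only if the replacement is unadjusted. It is then about 2 points or none with uninformative covariates, and roughly 6-24 points by formula if R² is .2-.4, with smaller losses in simulation. These figures rest on assumed R² values, an assumed score and simulated response shapes, so they should not be read as a forecast that power will fall.

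The case for change rests mainly on two facts: the check gives ANCOVA no protection that it needs, and leaving the choice open allows selection among tests. It is worth correcting before any outcome data are examined.

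**What to change.** In Statistical analyses, state that the normality check does not apply to hypothesis 5. For intention, the primary test is ANCOVA with its covariates listed by name and with heteroscedasticity-robust or bootstrap standard errors, whatever the distribution looks like. Name one rank-based or ordinal analysis (for example rank ANCOVA or a proportional-odds model) as a sensitivity analysis that does not replace the primary result. State how the three intention items are scored. For action, specify logistic regression.

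The cost is a few sentences and an option in the software. The sample size, data collection and trial procedures are unaffected.

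### RQ1 may be tested by an ANOVA that compares mean levels, not two associations; and message arm, a possible common cause, is not listed in the RQ1 model

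*Protocol article*

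**What the plan says.** The Hypotheses section poses RQ1 as a question: "is there any difference between personal outcome expectations and family outcome expectations in their association with intention". The Statistical analyses section gives the method: "Research question 1 will be tested either using structural equation modeling (SEM) or ANOVA". It states no rule for choosing between the two. The entry for RQ1 in the same section reads: "Predictor variable: positive outcome expectations (personal vs family). Outcome: intention to undergo genetic test for BRCA germline mutations". It lists no covariate and no message arm. Hypotheses 1 to 4 list demographic and health-status covariates only. Arm is the predictor in Hypothesis 5, which is tested by ANCOVA.

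Under Positive outcome expectation, each man answers eight items, four about himself and four about his family. The Time 1 assessment section fixes the order. Risk perception, health risk aversion and intolerance of uncertainty come before randomisation. Then: "After this evaluation, participants will be randomized and exposed to one message". After the message, "positive outcome expectations, action self-efficacy, benefit for genetic test will be then collected". The Measures section puts the expectation items under a T2 label, but also after message exposure. The Intervention section says that one message explains benefits to the man himself and the other benefits to his family.

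**The concern.** RQ1 is about two slopes on one outcome. The permitted ANOVA has no factor that corresponds to it. With personal versus family as a within-person factor, it tests whether men score higher on one scale than on the other. With intention as the outcome, the two continuous scores would have to be cut into categories, and each would be tested against zero rather than against the other. The study could then report an answer to RQ1 that comes from a different question.

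The second issue is confounding by arm. The two messages differ on the same content that the two scales measure, and Hypothesis 5 expects the family message to raise intention. If both effects occur, and part of the effect on intention does not pass through the scales, a model without arm credits that part to the family scale. The error would run in the direction the authors expect, and so could be read as confirmation.

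**Working it through.** The plan gives no figure for RQ1, so there is none to reproduce. From the document come the two-scale measurement, the order of measurement, the RQ1 entry, the sample sizes 132 and 264 (both stand in the sample size section), and partial η² = .05. The last converts to f = √(.05/.95) = 0.229 and d = 2f = 0.459. Assumed, because the document gives no values: within-arm correlation of the two scales ρ = 0.5, equal true slopes b = 0.30, residual SD 0.8, and the shifts and direct effects shown below.

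**1. ANOVA against slope test.** Simulation, N = 132, 2,000 replicates. The ANOVA is the repeated-measures comparison of the two scale means. The slope test is the contrast b_family − b_personal in a regression of intention on both scores.

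| True state | ANOVA rejects | Slope test rejects |
|---|---|---|
| Equal slopes (0.3, 0.3), means differ by 0.3 SD | 93% | 5% |
| Slopes 0.1 and 0.5, equal means | 5% | 81% |

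The ANOVA responds to the means and is blind to the slopes. This result needs no assumption about the messages.

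**2. Leaving arm out of the RQ1 model.** Let z = +1 for the family message and −1 for the self message. Let each message raise its matching scale by s, so that F = e₂ + (s/2)z and P = e₁ − (s/2)z. Let intention = bP + bF + (d/2)z + error, where d is the effect of arm that does not pass through the scales. Then z is uncorrelated with F + P, and:

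- Var(F − P) = 2(1 − ρ) + s² = 1 + s² at ρ = 0.5
- Cov(F − P, (d/2)z) = sd/2
- bias in each slope = ±(sd/2)/(1 + s²), plus for family and minus for personal
- spurious gap = sd/(1 + s²)

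Results:

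- s = 0.4, d = 0.30: gap 0.12/1.16 = 0.103; slopes 0.25 and 0.35.
- s = 0.5, d = 0.46: gap 0.23/1.25 = 0.184; slopes 0.21 and 0.39.
- s = 0.3, d = 0.20: gap 0.06/1.09 = 0.055.
- d = 0 or s = 0: gap 0.

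**3. Consequence for the RQ1 test.** Simulation, 2,000 replicates per setting, equal true slopes, 5% level:

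| Setting | N = 132, no arm | N = 264, no arm |
|---|---|---|
| s = 0.3, d = 0 | 4.8% | 5.4% |
| s = 0.5, d = 0 | 5.5% | 5.2% |
| s = 0.3, d = 0.30 | 10.0% | 14.1% |
| s = 0.3, d = 0.459 | 14.4% | 25.4% |
| s = 0.5, d = 0.30 | 15.2% | 25.4% |
| s = 0.5, d = 0.459 | 29.2% | 53.1% |

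With arm in the model, the rejection rate was 4.3% to 5.6% in every setting and the mean estimated gap was about 0.

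**The case against.** The case against has four parts.

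- **SEM is already offered, and RQ1 is not the primary comparison.** Both are true. SEM can test equality of the two paths, and the message comparison in Hypothesis 5 is untouched. But the plan lets the analyst choose ANOVA, so the defect in the permitted alternative stands.
- **The size of the arm bias is assumed.** This stands. No document figure supports the shifts, the correlation or the slopes. Taking d = 0.459 treats the whole planning effect as bypassing the expectations. At s = 0.4 the standard error of the slope difference is 2 × 0.8/√(N × 1.16), which is 0.13 at N = 132 and 0.09 at N = 264. A gap of 0.10 is therefore only about 0.8 and 1.1 standard errors.
- **The omission of arm cannot be fully checked.** Fig 1, the tested model, is not shown, and the article condenses the full protocol. What can be said is that the RQ1 entry, as listed, has no arm term.
- **The arm argument is easily carried too far.** A reader might infer that no model contains arm, but Hypothesis 5 does. A reader might take it as given that the messages shift the scales. That is inferred from timing and content and is not stated. Nor does it touch risk perception, health risk attitude or intolerance of uncertainty, which are measured before randomisation.

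**Conclusion.** The ANOVA option does not answer RQ1 and can mislead in both directions. That conclusion rests only on the wording of RQ1 and on each man answering both scales.

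The arm point holds for RQ1 conditionally. The slope difference is biased towards the family scale if each message raises its own scale and the family message also raises intention by another route. Under the stated assumptions the gap is 0.055 to 0.18, with 0.10 as the middle case. If arm acts only through the two scales, there is no bias.

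A reader might also infer that Hypothesis 1 could be positive merely because of randomised exposure. The calculations do not show this. With equal opposite shifts, arm is uncorrelated with the sum of the scales, and the two distorted slopes still average 0.30. Hypothesis 2 is not confounded by arm, because its predictors precede randomisation. Hypotheses 3 and 4 have planning and action as outcomes, and no effect on them has been shown. The matter should be corrected, but it concerns a secondary question and does not threaten the main comparison.

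**What to change.** Delete ANOVA as an option for RQ1. Put both expectation scores on a common metric and enter them together in one regression or SEM for intention, with message arm and the covariates collected at T1 before the message. Test equality of the two coefficients by a Wald test, or by the chi-square difference between the constrained and unconstrained models.

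Adding arm to the Hypothesis 1 model is a sensible low-cost option, since that model has post-message predictors of intention. It is not needed to remove confounding for Hypothesis 2.

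The cost is a change of wording in the analysis plan and one extra model term. No new data are needed.
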